## Abstract

**Background:**

Infant colic, characterised by excessive crying/fussing for no apparent cause, affects up to 20% of infants under three months of age and is a great burden to families, health professionals and the health system. One promising approach to improving its management is the use of oral probiotics. The *Baby Biotics* trial aims to determine whether the probiotic *Lactobacillus reuteri DSM 17938* is effective in reducing crying in infants less than three months old (<13.0 weeks) with infant colic when compared to placebo.

**Methods/Design:**

*Design:* Double-blind, placebo-controlled randomised trial in Melbourne, Australia. *Participants:* 160 breast and formula fed infants less than three months old who present either to clinical or community services and meet Wessel’s criteria of crying and/or fussing. *Intervention:* Oral once-daily *Lactobacillus reuteri* (1x10^8^ cfu) versus placebo for one month. *Primary outcome:* Infant crying/fussing time per 24 hours at one month. *Secondary outcomes:* i) number of episodes of infant crying/fussing per 24 hours and ii) infant sleep duration per 24 hours (at 7, 14, 21, 28 days and 6 months); iii) maternal mental health scores, iv) family functioning scores, v) parent quality adjusted life years scores, and vi) intervention cost-effectiveness (at one and six months); and vii) infant faecal microbiota diversity, viii) infant faecal calprotectin levels and ix) *Eschericia coli* load (at one month only). *Analysis:* Primary and secondary outcomes for the intervention versus control groups will be compared with t tests and non-parametric tests for continuous data and chi squared tests for dichotomous data. Regression models will be used to adjust for potential confounding factors. Intention-to-treat analysis will be applied.

**Discussion:**

An effective, practical and acceptable intervention for infant colic would represent a major clinical advance. Because our trial includes breast *and* formula-fed babies, our results should generalise to most babies with colic. If cost-effective, the intervention’s simplicity is such that it could be widely taken up as a new standard of care in the primary and secondary care sectors.

**Trial Registration:**

Current Controlled Trials ISRCTN95287767

## Background

### The burden of infant colic

Infant colic, characterised by excessive crying/fussing for no apparent cause, is common and distressing to families. Infant colic is defined clinically by Wessel’s criteria of crying and/or fussing ≥3 hours/day for ≥3 days/week for ≥3 weeks [1]. In research, the modified Wessel’s criteria of crying and/or fussing ≥3 hours/day for ≥3 days/week for one week is used for practicality and feasibility, due to the natural course of infant colic symptoms appearing by around three weeks, peaking at eight weeks, and remitting beyond 12 weeks of a term infant’s chronological age. Infant colic affects up to 20% of infants under three months [2,3].

Infant colic poses a great burden to families, health professionals and the health system. Early infant sleeping and crying problems are the most common reason parents seek health professional help in the first three months of life, costing an estimated £65 million pounds per annum in the UK in 2001 [4]. Infant colic has significant adverse effects on maternal mental health and family quality of life [5,6] and is a trigger for child abuse [7,8]. Infants in whom crying persists beyond three months are at risk of adverse outcomes in the school years including anxiety, aggression, hyperactivity, allergy, and sleep disorders [9,10], and at more than double the risk of poor mental health in later years [11]. Families of infants with colic are more dissatisfied with their daily family functioning in later years [12].

After 50 years of research into infant colic, its aetiology remains unclear and evidence-based management options limited. Finding an effective management strategy for infant colic could significantly reduce its associated morbidities and improve the quality of life of many families.

### Proposed aetiological factors for infant colic

Debate continues around whether infant colic represents an extreme of the spectrum of normal crying, or a manifestation of underlying physiological or psychosocial factors. Perhaps, infant colic is best thought of as an exacerbation of infant crying with the aggravation brought about by either physiological factors within the infant, or psychosocial issues with the mother and infant [13]. Proposed psychosocial theories include difficult infant temperament, immaturity in the infant’s ability to modulate reactions to internal and external stimuli, inadequate maternal-infant interaction and maternal anxiety [13]. Physiological theories are based on gastrointestinal factors, including gut dysmotility, excessive intragastrointestinal air, and visceral pain [14,15]. However, no study has been able to definitively prove whether these are causal factors of infant colic. Gastro-oesphageal reflux was traditionally assumed to be a cause of infant distress, but several recent clinical trials have demonstrated that it is an unlikely cause for persistent crying [16,17]. Food allergy is perhaps the strongest factor identified so far in the causal pathway to crying [18-22], with gut inflammation resulting from allergy to cow’s milk protein assumed to be the underlying mechanism. Faecal calprotectin, a gut inflammatory marker, has been identified to be higher in infants with colic compared to those without in one study [23], although another study did not confirm this finding [24]. Another possible mechanism may be an alteration of gut microbiota in infants with cow’s milk protein allergy [25,26].

Recent research has focussed on the pathophysiological role of gut microbiota in the exacerbation of infant crying. This promising new hypothesis is currently generating substantial research interest, with several studies confirming differences in gut microbiota between infants with and without colic. One study indicated increased concentrations of faecal *Clostridium difficile* in infants with colic compared to controls [27], while two studies reported increased *Eschericia coli* (*E coli*) concentrations and reduced *Lactobacillus* species concentrations in infants with colic compared to controls [28,29]. Another study identified certain *Lactobacillus* strains to predominate in infants with colic compared to controls [30], while a more recent study suggested certain *Bifidobacterium* and *Lactobacillus* species to be protective against crying [31]. These findings suggest that while the microbiota are likely to be different in infants with colic, it remains uncertain whether these microbiota differences are the cause or result of the colic condition. Disturbances in gut microbiota may lead to mechanical changes in the gut, such as gas production and bloating and/or gut dysmotility [32,33], which in turn lead to infant crying. The aetiology of infant colic is likely multifactorial.

### Current treatment options for infant colic

Four systematic reviews have evaluated the effectiveness of interventions for infant colic [34-37]. The best evidence supports the use of hypoallergenic or extensively hydrolysed whey or casein-based formula in infants, and instigating maternal elimination diets in breastfeeding mothers, supporting the role of food allergy as a cause of persistent infant crying. However, elimination of cow’s milk from breastfeeding mothers is not always effective and it is unclear which babies respond to hypoallergenic diets and which do not. Other possible effective strategies include improved parental responsiveness, reduced stimulation and the use of sucrose. Ineffective strategies include focused parental counselling, increased carrying, use of car ride stimulators, soy milk and fibre enriched diets. Proton-pump inhibitors for presumed gastrooesophageal reflux disease are ineffective [17]. Simethicone, an anti-foaming agent used to reduce intragastrointestinal gas and bloating, is also ineffective [38,39]. Anticholinergic drugs such as dicyclomine are effective but are associated with significant adverse effects in infants [2,35]. Providing families with support is effective in reducing caregiver stress, but effects on crying are inconclusive [34]. There are therefore no effective and feasible strategies that can be easily implemented to help families with infants with colic.

### Use of probiotics and the potential role of *Lactobacillus reuteri* in infant colic

One promising new approach to the management of infant colic is the use of probiotics. Probiotics are live microorganisms believed to confer health benefits and are used widely in food products, including infant formulae [40]. Probiotics colonise the bowel, competitively inhibit other bacterial adhesion, stimulate host immune responses to pathogens, suppress intestinal inflammation, increase mucus layers and strengthen mucosal barriers [41-43]. Probiotics can modulate infant gut microbiota and increase microbiota diversity [44-52]. A recent study demonstrated specific *Lactobacillus* strains were able to inhibit the growth of gas-producing coliforms isolated in infants with colic [32]. Probiotics and prebiotics have also been shown to alter gastrointestinal motility in newborns by stimulating gastric emptying [33]. Animal studies have shown probiotics to change pain perception mediated by the gut and inhibit gut contractile activity in rats [53-59]. Another explanation is that probiotics may reduce gut inflammation, from whatever cause, in turn reducing associated infant distress.

Four randomised controlled trials have examined the therapeutic effects of probiotics in treating infant colic. In 2007, Savino et al. reported a significant benefit in the use of *Lactobacillus reuteri* (*L reuteri*) strain ATCC 55730 in the treatment of infant colic when compared with simethicone (n = 83) [60]. This study was replicated in 2010 using *L reuteri* strain DSM17938 as the intervention and a placebo (n = 50), with similar promising results [61]. Both studies involved only exclusively breastfed infants whose mothers were all on cow’s milk-free diets. Two other trials using different mixtures of probiotics investigated their therapeutic effects on infant colic (n = 9, n = 62) [52,62] and concluded there were no significant effects on crying time.

The mixed results in the above studies mean that the role of probiotics (including *L reuteri*) in the treatment of infant colic remains uncertain. Moreover, the findings may not necessarily be applicable to the general population since in both the Savino et al. trials, the study populations were restricted to breastfed infants whose mothers were on a cow’s milk-free diet (a select group that is not representative of the general population). Furthermore, there are methodological concerns regarding the previous studies that require further investigation. For example, the comparison group in the 2007 Savino et al. study was simethicone rather than a placebo, which meant that the interventions could not be blinded due to differences in dosage and time of administration. The other trials lacked sufficient power to detect differences and used combinations of probiotics, which can contribute to varying results since probiotic bacteria are known to have species specific effects [52,62]. In summary, there is insufficient evidence to recommend the use of probiotics in infant colic.

### Aims and hypotheses

This double-blind, placebo-controlled randomised trial aims to determine whether the probiotic *L reuteri DSM 17938* benefits infants <3 months old (<13.0 weeks) with colic by reducing daily duration of infant crying/fussing. Secondary aims are whether there is reduced daily frequency of episodes of infant crying/fussing, and improved infant sleep, maternal mental health, and parent and family functioning. We also aim to investigate changes in gut microbiota, faecal calprotectin and *E coli* colonisation which are all possibly implicated in the mechanism of disease, and finally to determine whether probiotic use reduces healthcare costs in infant colic.

We hypothesise that, compared to the placebo (control) group, the *L reuteri* (intervention) group will have lower daily crying/fussing time per 24 hours at one month post randomisation. We further hypothesise that the *L reuteri* (intervention) group at 7, 14, 21, 28 days and 6 months post randomisation will have:

• lower crying/fussing time per 24 hours,

• fewer crying/fussing episodes per 24 hours,

• longer sleep duration,

• higher scores on a standardised measure of maternal mental health (one and six months),

• higher scores on a standardised measure of family functioning (one and six months), and

• higher scores on a standardised measure of parent quality adjusted life years (one and six months).

We also hypothesise that the intervention group compared to the control group will have (at one month):

• more diverse gut microbiota,

• lower faecal calprotectin levels, and

• less *E. coli* colonisation, thereby suggesting a potential pathophysiological mechanism in infant colic.

Finally, we hypothesise that the intervention will be potentially cost-saving to the health care system by diverting families away from more expensive management such as overnight stays at mother-infant units.

## Methods/Design

### Study design, setting and participants

This is a phase III, double-blind, randomised placebo-controlled trial drawing on clinical and community based samples. The trial has been approved by the Royal Children’s Hospital Human Research Ethics Committee (HREC 30111).

Recruitment is from a range of services widely used by and readily accessible to parents seeking medical advice regarding their crying babies in Melbourne, Australia. These comprise: the Royal Children’s Hospital Emergency Department (RCH ED), the RCH Unsettled Babies clinic (a tertiary referral-based clinic for assessment and management of unsettled babies), Tweddle Child and Family Health Centre (a mother-infant parenting centre), two Maternal Child Health centres (universal nurse health checks in the Boroondara and Moonee Valley districts), and paediatricians at the RCH and in private practices. Interested families can also directly contact the study team to be involved.

A total sample of 160 infants less than three months (13.0 weeks) old with infant colic is being recruited between August 2011 and August 2012. The expected total duration of the study from the start of recruitment to the last subject finishing the six month follow-up is 18 months. The treatment period is one month, with a follow-up period of six months.

### Inclusion criteria

Each infant must meet all of the following criteria to be enrolled in this study:

1. Infant colic, i.e. crying or fussing ≥ 3 hours/day for ≥ 3 days over seven days (as defined by the modified Wessel’s criteria) by caregiver’s report at the time of study commencement;

2. Less than three months (i.e. up to and excluding 13.0 weeks) old at the time of study commencement;

3. Greater than 36 weeks gestation at birth; and

4. Birth weight of more than 2500 g.

### Exclusion criteria

Infants meeting any of the following criteria are excluded from the study:

1. Failure to thrive (weight gain < 100 grams/week averaged from birth to the last recorded weight);

2. Major medical problems (eg. ill, immunocompromised, major developmental or genetic abnormality);

3. Taking solids, antibiotics or *L reuteri* and, if breastfeeding, has mother taking *L reuteri* at the time of study commencement;

4. Cow’s milk protein allergy, defined as resolution of crying after a paediatrician-recommended two week trial of dairy-free diet in the infant, or in the mother if breast-feeding, at the time of study enrolment; and

5. Caregiver has insufficient English to understand informed consent and complete questionnaires.

### Randomisation

A block randomisation schedule to maintain balance between treatment arms has been prepared by an independent statistician, not directly involved in the analysis of the study results, from the Clinical Epidemiology and Biostatistics Unit (CEBU) at the RCH and supplied to Pharmacy who dispense the study product. Randomisation is stratified by method of infant feeding (breastfed versus formula-fed) and age at the time of study commencement (≤6 weeks versus >6 weeks, due to the natural crying peak occurring at around six weeks of age). Infants on a mixture of both breast- and formula-feeding are allocated to the formula-fed stratum. To minimise potential biases, the study is double-blind whereby treatment allocation is concealed from all study investigators and participants.

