Regression models will be used to estimate treatment effect sizes, odds ratios and 95% confidence interval, adjusting for potential confounding factors identified a priori and measured at baseline. These include infant age (≤6 weeks versus >6 weeks, taking into account the natural course of infant colic symptomatology with the peak of crying at six weeks), mode of birth delivery, maternal smoking, use of antibiotics or probiotics in infants and breastfeeding mothers, maternal diet if breastfeeding, maternal mental health scores, and known causes of crying (e.g. fever, eczema, vaccination, vomiting, and diarrhoea). Random effects regression models will be used for further longitudinal analysis examining trends in crying time within individual babies.

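### Two different peak ages for colic crying are given (eight and six weeks), and the adjusted model reduces age to a six-week split: a small, avoidable loss of precision, not a bias

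*Protocol article*

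**What the plan says.** In the protocol article, The burden of infant colic (Background) describes colic symptoms as "appearing by around three weeks, peaking at eight weeks, and remitting beyond 12 weeks" of age.

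Randomisation stratifies by feeding method and by "age at the time of study commencement (≤6 weeks versus >6 weeks", giving as the reason "due to the natural crying peak occurring at around six weeks of age".

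The regression paragraph of Data analysis lists the baseline adjustment factors chosen in advance: "These include infant age (≤6 weeks versus >6 weeks", justified as "taking into account the natural course of infant colic symptomatology with the peak of crying at six weeks". Age is one of several factors there, and the split is the only form of age named.

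The Inclusion criteria admit infants "Less than three months (i.e. up to and excluding 13.0 weeks) old at the time of study commencement". The primary outcome is crying time per 24 hours at day 28. Groups are compared by t test or a non-parametric test, and the regression models supply the adjusted estimates.

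**The concern.** The stated reason for a design cut disagrees with the document's own account of the condition. The Background and the regression paragraph both speak of the course of colic symptoms, so a distinction between normal crying and colic does not explain the gap.

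The form of the covariate is a separate matter. It is fixed in the text, not left open. The older group runs from just over 6 to just under 13 weeks at entry, so from just over 10 to just under 17 weeks at day 28. An infant entering at 7 weeks is measured at 11 weeks and one entering at 12 weeks at 16 weeks, yet both carry the same age code. If crying falls with age over this span, some explainable variance stays in the residual, and a chance age difference between arms within the stratum is neither balanced by design nor corrected by the model. What is at stake is precision and protection against chance imbalance in the adjusted estimate.

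**Working it through.** **1. The plan's own figure.** Inputs from Estimation of sample size: effect 0.5 SD, 80% power, significance level 0.05 (two-sided assumed), 20% dropout, equal arms assumed. Normal approximation: 2(1.960 + 0.842)²/0.5² = 62.8, so 63 per arm, 126 in all, and 126/0.8 = 158 after rounding up. The t-test version gives 64 per arm, 128 in all, and 128/0.8 = 160. The stated 160 is reproduced, and it uses no age term.

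**2. Age information kept by the six-week split.** The article gives no entry-age distribution. Assume uniform ages from L to 13 weeks, with L = 2, 3 or 4.

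*Linear age effect.* With p = (6 − L)/(13 − L), the share of age-explained variance kept is 3p(1 − p):
- L = 2: p = 4/11, share 69%
- L = 3: p = 3/10, share 63%
- L = 4: p = 2/9, share 52%

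The loss is 31–48%.

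*Background course.* Take a curve that is zero at 3 weeks, rises linearly to a peak at 8, falls linearly to zero at 12 and stays there. Read it at entry age + 4 weeks. The share kept is the squared correlation between the curve and the split:

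| L (weeks) | Six-week split, day 28 | Eight-week split, day 28 |
|---|---|---|
| 2 | 86% | 67% |
| 3 | 85% | 64% |
| 4 | 81% | 63% |

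The loss at day 28 is 14–19%. The same curve read at earlier times gives shares for the six-week split of 2–18% at entry, 0–5% at day 7, 21–34% at day 14 and 63–69% at day 21.

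**3. What this costs in power.** With 160 × 0.8/2 = 64 completers per arm, and age explaining a fraction R² of outcome variance of which a share s is captured:

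power = Φ(0.5·√(64/2)/√(1 − R²s) − 1.96)

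Without adjustment this is Φ(2.828 − 1.96) = 80.7%. R² is not in the article; 5–20% is an assumption. The last four columns show the points lost against full adjustment:

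| R² | Full adjustment (s = 1) | s = 0.86 | s = 0.81 | s = 0.63 | s = 0.52 |
|---|---|---|---|---|---|
| 5% | 82.7% | 0.3 | 0.4 | 0.7 | 0.9 |
| 10% | 84.6% | 0.5 | 0.8 | 1.4 | 1.9 |
| 20% | 88.5% | 1.1 | 1.5 | 2.9 | 3.7 |

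With ages from 3 weeks (s from 0.63 to 0.85) the loss is about 0.3 to 2.9 points. Power with the two-level term stays above 80% in every cell.

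**4. Would a continuous term do better?** Shares of day-28 variance captured under the Background curve, for L = 2, 3, 4:
- linear term alone: 80%, 81%, 74%
- linear plus quadratic: 84%, 94%, 98%
- restricted cubic spline, four knots at the 5th, 35th, 65th and 95th centiles: 93%, 96%, 99%

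A straight line alone does worse than the split on this curve. The quadratic beats it except when ages reach down to 2 weeks. The spline beats it in all three cases.

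**The case against.** The best defence is that the six-week split serves the primary outcome well even if the peak is at eight weeks. The outcome is read four weeks after entry, and on the Background's own curve a six-week split captures more of the day-28 variance than an eight-week split. That stands: moving the cut to eight weeks would not help at day 28.

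The older group is also less mixed than its age span suggests. Everyone entering at 8 weeks or later is past 12 weeks at day 28; under uniform ages only 2/7 (29%) of that group are not, and they are then 10 to 12 weeks old. This too stands, and it is why the loss under that curve is modest.

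Adjusting for a stratification factor in the form used to stratify is accepted practice. That is fair: the two-level term is less efficient, not an error.

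A reader might infer that the split throws away the main predictor of crying, or that it biases the comparison. The document supports neither. Age remains both a stratum and a covariate, most of its day-28 signal can survive the split, the article lists age among several factors without ranking it, and randomisation protects the comparison from systematic bias. Nor can a defect be claimed in the random effects models, since the article names no form of age for them.

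The defence does not remove the inconsistent peak age, and it shows only that the gain from a finer age term is small.

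**Conclusion.** The point holds as a minor one. The peak age is stated as eight weeks in the Background and as six weeks in Randomisation and in the regression paragraph, and the adjusted model fixes age as the six-week split. The split coarsens a relevant baseline predictor and leaves chance age imbalance within the older group unadjusted.

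The size rests on three assumptions that the article cannot confirm: uniform entry ages, the shape of the age curve, and age explaining 5–20% of outcome variance. The power losses are measured against an ideal adjustment that captures all the age signal, so they are upper limits for what any practical age term could recover. No stated figure is wrong because of this.

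The choice of natural history matters more for the secondary crying outcomes at days 7 and 14, where the split carries little age information if the Background's course is right.

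**What to change.** - Reconcile the peak age across The burden of infant colic, Randomisation and the regression paragraph, so that the reason for the cut agrees with the stated natural course.
- Leave the randomisation strata as they are.
- In the adjusted regression, replace the two-level age term with age at randomisation as a continuous covariate with a prespecified non-linear term. A spline with fixed knots is the safer choice; a quadratic is acceptable if few infants enter before 3 weeks. A linear term alone should not be used.
- If age enters the longitudinal models, use the same form there.

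The cost is a change of wording and one extra model degree of freedom for the quadratic, or two for a four-knot spline. Age has to be known for eligibility and stratification, so no new data are needed and the sample size stays at 160.
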